### Statistical analyses

Prior to analyses, we will exclude participants based on the following criteria to decrease noise in online survey data: relative speed indicator higher than 2, which means that the respondent has completed a page twice as fast as a typical respondent [70], and a completion time < 5 min, which means an unrealistic absolute completion time. To deal with missing data and drop-out, multiple imputations via fully conditional specification implemented by the MICE algorithm will be used [71].

We will apply cross-lagged panel models to estimate the reciprocal relationships between a) resiliency and coping strategies and b) psychosocial adaptation and adjustment. Dependent measures will be checked for normality and then centered based on their grand mean. As a first step, we will conduct longitudinal confirmatory factor analyses (CFA) for each cohort (“inconspicuous”; “conspicuous”), using the covariance matrix. In a second step, we will specify longitudinal cross-lagged panel models with a) resiliency and coping strategies and b) psychosocial adaptation and adjustment as latent factors for each group. In a third step, we will conduct a multigroup analysis, which combines the models for both cohorts. In a fourth step, we will implement the covariates (e.g., age, gender) into the final models. In a final step, we will split latent predictors into their respective indicators examining the relations between a) resiliency and coping strategies and b) psychosocial adaptation and adjustment at the level of components.

Regression analyses will be applied to analyze the incremental/additional contribution of adaptation in psychosocial adjustment beyond the influence of general demographic and CC-related factors. HRQoL (total score and subscales’ scores) will serve as dependent variable(s), the sociodemographic, CC-specific risk factors and the psychosocial adaptation will form the independent variables. The analysis on differences in a) resiliency and coping strategies and b) the psychosocial adaptation and adjustment depending on demographic and CC-related factors will be addressed by three multifactorial ANOVAs. To examine differences in the course of psychosocial adaptation and psychosocial adjustment, multifactorial repeated measures ANOVAs will be applied. Before these analyses (Hypotheses 2–4), data will be checked on homoscedasticity, normal distribution of errors and multicollinearity. We will control for overall Covid-19 related distress for all analyses, if there is a significant association with psychosocial adjustment at T1 and/or T2. The analyses will be conducted using R [71–74].

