#### HRQoL

HRQoL is one of the major outcomes in medical research and is measured by the German version of the DISABKIDS Chronic Generic Module (DCGM-37) [35]. The 37 items are allocated to three domains with two facets each: psychological (independence, emotions), social (social exclusion, social inclusion), and physical (physical limitations, treatment/medication). The items are measured on a 5-point Likert scale ranging from 1 “never” to 5 “always”. A sample item is: “Do you have fun in your life?”. Internal consistency of the subscales ranges from Cronbach’s α = .70 to Cronbach’s α = .87. Internal consistency for the total score is Cronbach’s α = .93 [35].

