#### Resources in childhood and youth

Seven of the ten subscales of the Questionnaire of Resources in Childhood and Youth (FRKJ 8–16) are used to assess personal (empathy and perspective-taking, self-efficacy, self-esteem, optimism, and sense of coherence) and social resources (parental and social support, peer-group integration) in children and adolescents [42]. Each subscale contains six items. Participants’ responses are measured on a scale ranging from 1 “never true” to 4 “always true”. A sample item is: “When I set my mind to something, I get it done.”. The reliability of the subscales ranges from Cronbach’s α = .69 to Cronbach’s α = .89 [42].

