#### Self-compassion

The German version of the Self-Compassion Scale (SCS-D, short version) encompasses 12 items rated on a 5-point scale, ranging from 1 “almost never” to 5 “almost always” [46] and comprises six subscales: self-kindness, self-judgment, common humanity, isolation, mindfulness, over-identification. A sample item is: “I try to be understanding and patient towards those aspects of my personality I don’t like.”. Internal consistency for the subscales ranges from Cronbach’s α = .54 to Cronbach’s α = .75 (total score: Cronbach’s α = .86) [47].

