#### Coping with chronic health conditions

The German version of the 29-item Coping with Chronic Health Conditions Questionnaire (CODI) is used to assess coping strategies of children and adolescents with CCs [49]. The CODI comprises six domains: acceptance, avoidance, cognitive-palliative, distance, emotional reaction, and wishful thinking. Participants indicate their use of the coping strategies on a 5-point Likert scale ranging from 1 “never” to 5 “all the time” (e.g., “I try to ignore my illness.”). Depending on the domain, the internal consistency of the questionnaire ranges from Cronbach’s α = .69 to Cronbach’s α = .83 [49].

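### The component-level step, as ordinarily read, drops the measurement-error correction of the latent models, so component coefficients are not comparable and apparent reciprocity can be an artefact

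*Protocol article*

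**What the plan says.** The Statistical analyses section of the Protocol article sets out a sequence: longitudinal confirmatory factor analyses per group, cross-lagged panel models with "psychosocial adaptation and adjustment as latent factors for each group", a multigroup model, and covariates. It then states: "In a final step, we will split latent predictors into their respective indicators". The purpose is to study the relations between resiliency and coping, and between "psychosocial adaptation and adjustment at the level of components". No error term or reliability correction is given for this step.

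The measures sections give these reliabilities:

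- Resources (FRKJ 8–16): "The reliability of the subscales ranges from Cronbach’s α = .69", up to .89.
- Coping (CODI): "the internal consistency of the questionnaire ranges from Cronbach’s α = .69", up to .83.
- Emotion regulation (ERQ): .76 and .74.
- Self-compassion (SCS-D): "Internal consistency for the subscales ranges from Cronbach’s α = .54 to Cronbach’s α = .75 (total score: Cronbach’s α = .86").
- Health-related quality of life (DCGM-37), an adjustment measure: "Internal consistency for the total score is Cronbach’s α = .93".

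**The concern.** A latent cross-lagged model separates true score from error. An observed-score model does not, and two things follow.

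First, a component measured with more error shows a smaller path to later adjustment than an equally important component measured with less. The coefficients then partly describe the questionnaires.

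Second, error in a component at T1 means that its own earlier level is under-controlled. Part of its stability is then credited to whatever correlates with it at T1, including adjustment. This appears as a path from adjustment at T1 to the component at T2, even where none exists.

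The first research question under Objectives concerns reciprocal influence and which construct precedes the other. For a less reliable scale both distortions work in the same direction: the outgoing path is weakened and the incoming one is inflated. A reader of the component results could therefore see a reciprocal or reversed relation that comes from measurement error alone.

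**Working it through.** **No plan figure to reproduce.** The Sample size section rests on a rule of thumb and gives no effect size or power, so there is no stated precision for this step.

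**Inputs from the Protocol article.** Component alphas of .69 and .89 (FRKJ 8–16), .86 (SCS-D total) and .54 (lowest SCS-D subscale); outcome reliability .93 (DCGM-37 total). Sample sizes: 129 (conspicuous) and 426 (total) in Table 1, and 200 per group from the Sample size section.

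**Assumptions not in the article.** True T1 correlation c between component X and adjustment Y, true stability s, a two-variable model, alpha taken as the reliability, and a two-sided 5% test.

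**Outgoing path X(T1) → Y(T2), true value .20, c = .5, s = .6.** Let a be the reliability of X. The observed correlations are:

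- r(X1,Y1) = .5·√(a·.93)
- r(X1,Y2) = (.20 + .6·.5)·√(a·.93)
- r(Y1,Y2) = (.6 + .20·.5)·.93 = .651

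The observed path is [r(X1,Y2) − r(Y1,Y2)·r(X1,Y1)] / [1 − r(X1,Y1)²].

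- a = .69: r(X1,Y1) = r(X1,Y2) = .4005, so (.4005 − .651·.4005)/(1 − .1604) = .166.
- a = .89: both are .4549, so (.4549 − .651·.4549)/(1 − .2069) = .200. Here error in the outcome's own baseline offsets the attenuation.
- a = .54: .141.

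**Incoming path Y(T1) → X(T2), true value 0, c = .5, s = .7.** The observed correlations are:

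- r(X1,Y1) = .5·√(a·.93)
- r(X1,X2) = .7·a
- r(Y1,X2) = .7·.5·√(a·.93)

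The false path is [r(Y1,X2) − r(X1,X2)·r(X1,Y1)] / [1 − r(X1,Y1)²].

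For a = .69 this is (.2804 − .4830·.4005)/(1 − .1604) = .0869/.8396 = .104. With R² = .242, SE = √[(1 − R²)/((1 − r(X1,Y1)²)(n − 3))].

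| n | SE | z | rejected at 5% |
|---|---|---|---|
| 129 | .085 | 1.22 | 23% |
| 200 | .068 | 1.53 | 33% |
| 426 | .046 | 2.24 | 61% |

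For other reliabilities under the same assumptions:

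- a = .54: .130, rejected 32%, 46% and 78% at these three sizes.
- a = .86: .055, rejected 14% at n = 200 and 24% at n = 426.
- a = .89: .044, rejected 18% at n = 426.

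**Sensitivity at a = .69.** With c = .3 and s = .5 the false path is .040 (rejected 9% at n = 200). With c = .7 and s = .7 it is .177 (67% at n = 200).

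**Comparing two components.** Suppose both have a true effect of .15 and correlate .5 with each other and with baseline adjustment, outcome stability is .6 and outcome reliability .93. With reliabilities .69 and .89 the observed paths are .126 and .169. The more reliable scale shows the larger path in 69% of samples at n = 200, against 50% if error played no part. With reliabilities .86 and .89 the paths are .151 and .158 (53%).

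**The case against.** The strongest reply is that the observed-score model is inferred. The article does not say whether components enter as sum scores, as narrower factors built from items, or as error-corrected single indicators, and a fuller plan may settle this. That is fair. Still, the text names the indicators of the latent factors and states no correction, so a reader who follows it would use observed scales. One clause would resolve it.

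Several stronger readings are tempting and are not supported:

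- **A distorted ranking of components.** No ranking is planned. What is at risk is the comparison of coefficients.
- **A component range of .54 to .93.** The .93 belongs to an adjustment measure; resource and coping scales stop at .89. The .54 applies only if the SCS-D subscales are the indicators. Table 2 lists the SCS-D as one measure, and its total has alpha .86, so the subscales may never be used. The FRKJ and CODI floor of .69 does not depend on this.
- **False paths in both directions.** A truly null path from a .54 scale to an outcome measured at .93 is only about .02 (c = .5, s = .7). The large false paths run into the less reliable scale. If splitting the predictors means only that T1 components predict adjustment, those paths are not estimated and uneven attenuation is what remains.
- **Rejection rates for the pooled sample.** The 426 is a preliminary total, before drop-out and the speed exclusions, and the models are first fitted per group. The rates at 129 and 200 are closer to that use.

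**Conclusion.** The point holds for the last, component-level step, on the ordinary reading that indicators are observed scales. The latent models that precede it, which answer the construct-level question, are unaffected.

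At the firmly stated floor of .69 the outgoing attenuation is moderate (.20 becomes .17). The false incoming path ranges from about .04 to .18 over the assumed correlations (.3 to .7) and stabilities (.5 to .7), with .10 in the middle case. All sizes depend on those assumptions, on a two-variable simplification of the joint model, and on published alphas that may differ in this sample. The direction of the false path does not change over that range.

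This is a cheap improvement to a follow-up step. It does not invalidate the main analysis.

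**What to change.** Add to the final step of the Statistical analyses section wording such as: *Each component will be modelled as a latent variable with its items or parcels as indicators, or as a single indicator with error variance fixed at (1 − reliability in this sample) × observed variance, at T1 and T2. The SCS-D will enter as its total score. Component coefficients from uncorrected observed scores will not be compared with one another or used to infer reciprocity.*

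In simulation of the null incoming-path scenario, the fixed-error model brings the path back to about zero. The cost is modest extra modelling and a real loss of precision: standard errors about 1.3 times larger at alpha .69 and 1.5 times larger at .54. If that is judged too much at the achieved group sizes, the alternative is to label the step exploratory and report the components without comparing their coefficients.

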
## Objectives

The primary aim of the project is to get a deeper understanding of the dynamic process of psychosocial adaptation, including intra- and interpersonal resiliency and coping strategies, in the face of CCs in a group of adolescents (12–21 years) with type 1 diabetes, cystic fibrosis, and juvenile arthritis. Hereby, psychosocial adaptation refers to the process of adaptation, while psychosocial adjustment refers to the outcome of this adaptation process [13, 24]. The research questions (Q) and hypotheses are as follows:
Q1. How is the causal relationship between a) resiliency and coping strategies; b) psychosocial adaptation and adjustment? It is hypothesized that resiliency and coping strategies show reciprocal influences, and both precede the psychosocial adjustment.Q2. Does psychosocial adaptation (e.g., resilience factors and coping strategies) play a significant role in psychosocial adjustment beyond the influence of general demographic and CC-related factors? It is hypothesized that psychosocial adaptation is more important in explaining adjustment than the above-mentioned general factors (e.g., age, CC severity, gender). It is further assumed that females, as well as those showing conspicuous mental health screening, exhibit lower scores in psychosocial adjustment and therefore represent a high-risk group.Q3. Depending on general, demographic, and CC-related factors, do adolescents differ in psychosocial adaptation and adjustment? It is hypothesized that adolescents with higher age, female gender, more severe mental health problems and higher CC severity exhibit lower scores in psychosocial adaptation and adjustment.Q4. Depending on general, demographic, and CC-related factors, do adolescents differ in their course of psychosocial adaptation and adjustment over the one-year follow-up period? It is hypothesized that adolescents with higher age, female gender, more severe mental health problems and higher CC severity show a less favorable course of adaptation over the 1-year follow-up period compared to those with younger age, male gender, less severe mental health problems and lower CC severity. Figure 1 displays the conceptual model of the study.

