## Methods/design

### Study design

This prospective observational study is part of a consortium (Chronic Conditions in Adolescents: Implementation and Evaluation of Patient-centered Collaborative Healthcare (COACH)) funded by the German Federal Ministry of Education and Research (no. 01GL1740C) that examines the mental health status of adolescents with a CC and examines different approaches to understand and overcome mental health issues [25, 26]. The study received approval by the Ethics Committee of the University of Potsdam (date 02/02/2018, no. 52/2017; date 08/31/2018, no. 37/2018; date 10/22/2018, reference no. 37/2018). Assessments take place starting with the mental health screening in clinical units, followed by two assessment time points over 1 year if adolescents agree to participate in the study: baseline (T1) and 12 months follow-up (T2). Based on the mental health screening for anxiety and depression, participants are assigned into the two parallel groups “inconspicuous” with scores below the cut-off (GAD-7 and PHQ-9 < 7) and “conspicuous” with scores above the cut-off (GAD-7 or PHQ-9 ≥ 7) [27–31]. During the recruitment we have been confronted with the Covid-19 pandemic and several regulations to contain the spread of the SARS-CoV-2 coronavirus. Therefore, we included an additional online survey to monitor the Covid-19 pandemic effects. The Covid-19-specific study received approval by the Ethics Committee of the University of Potsdam (date 04/29/2020, no. 27/2020; date 06/26/2020, reference no. 48/2020). The intermediate Covid-19-specific online survey was first implemented in April 2020 and sent out to all participants that had been included into the study up to this point. Since then, the questionnaire has been being sent to participants consecutively 1 week after completing the questionnaire at baseline (T1). The flow chart of the study design is shown in Fig. 2.

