### Recruitment

Consecutive recruitment for this ongoing trial started in June 2019 in clinical centres. Adolescents with type 1 diabetes, cystic fibrosis, or juvenile idiopathic arthritis are recruited during their regular check-up visits in hospitals, clinics, medical practices, and medical centres across Germany. These clinical institutions all take part in one of the following German patient registries, the National Paediatric Rheumatologic Database (NPRD) [32], the National Diabetes Registry (DPV) [33], or the Cystic Fibrosis (CF) Registry [34]. Eligible patients (and their parents) are informed about the research project by the treating physician at the clinical centre and eligible patients are screened for anxiety and depression. All participants and parents of participants under legal age (< 18 years) provide written informed consent prior to inclusion into the study. Informed consent is sent to the University of Potsdam and all further recruitment activities are conducted by researchers there. In the next step, participants are invited to take part in the prospective online survey, which means that they are contacted by phone and receive an invitation email with the link to the survey. If they do not complete the questionnaire, they are contacted by email and phone at set time intervals and reminded to participate. Furthermore, they receive monthly SMS greetings to increase study adherence. To monitor the Covid-19 pandemic effects, participants are invited to take part in an intermediate online survey. Survey data will be connected with the objective medical background data provided by the patient registries: diagnosis, CC severity, CC duration and CC-specific data, e.g., hemoglobin A1c (HbA1c), forced expiratory volume in 1 s (FEV1), and clinical juvenile arthritis disease activity score (cJADAS). Principles of good research practice, data, and participants’ privacy protection are strictly adhered to. For each successfully recruited participant, the respective clinical unit receives a financial compensation of 75€ for its recruitment effort. Participants receive gift coupons as compensation for their time at T1 (20€) and T2 (30€). The online survey started in August 2019 and has been recruiting participants consecutively since. See Table 1 for preliminary descriptive data on the sample.

**Table 1 Tab1:** Demographics of the preliminary sample

Variables	Total (***n*** = 426)	Inconspicuous (***n*** = 297)	Conspicuous (***n*** = 129)
Gender			

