Male	185	141	44
Female	240	155	85
Non-binary	1	1	0
Age			
*M* (*SD*)	15.41 (2.05)	15.36 (2.03)	15.53 (2.11)
Range	12–21	12–21	12–21
Subjective socioeconomic status^a^			
*M* (*SD*)	6.73 (1.38)	6.92 (1.39)	6.30 (1.27)
Scale range^b^	Middle range	Middle range	Middle range
Chronic condition			
Type 1 diabetes	316	214	102
Cystic fibrosis	28	21	7
Juvenile idiopathic arthritis	82	62	20

*Note. M* Mean; *n* Number of participants; *SD* Standard deviation; Last day of data inclusion: 01/06/2021

^a^ Missings: *n* = 16

^b^ Scale ranges from 1 to 10

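### Q3 and Q4 state graded hypotheses about age, symptom severity and condition severity but are assigned to ANOVAs, which as named imply categorised predictors; the plan should enter these as continuous terms

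*Protocol article*

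**What the plan says.** The Objectives section of the protocol article words Q3 as a gradient in three of its four predictors: "adolescents with higher age, female gender, more severe mental health problems and higher CC severity exhibit lower scores" in adaptation and adjustment. Q4 uses the same four predictors for the one-year course, and sets those with the less favourable profile against the rest, "compared to those with younger age, male gender, less severe mental health problems and lower CC severity".

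The Statistical analyses section gives Q2 to regression, with sociodemographic factors, condition-specific risk factors and adaptation as independent variables. For Q3 the method changes: the differences "will be addressed by three multifactorial ANOVAs". For Q4, "multifactorial repeated measures ANOVAs will be applied". The section does not list the factors of these ANOVAs, give levels for age or condition severity, or say whether diagnosis is a factor.

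The only cut-off in the article is a score of 7 on the PHQ-9 or GAD-7, which forms the conspicuous and inconspicuous groups (Study design). The registries supply "CC severity, CC duration and CC-specific data, e.g., hemoglobin A1c (HbA1c), forced expiratory volume in 1 s (FEV1") and the cJADAS (Recruitment). A subjective severity rating is also collected (Sociodemographic and CC-specific information).

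**The concern.** Age (12–21 years) and the PHQ-9 and GAD-7 sums are graded scores, and so are the registry markers of severity. A multifactorial ANOVA is a method for crossed categorical factors. The move from regression in Q2 to ANOVA in Q3 and Q4, together with the group-contrast wording of Q4, makes categorised predictors the natural reading.

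Three things are at stake:

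- Categorising a graded predictor discards information and so lowers power for the hypothesis as worded.
- The result then depends on where the cut falls, and the article fixes no cut for age or condition severity. HbA1c, FEV1 and cJADAS share no unit, so one numerical cut could not serve all three conditions.
- Crossing many factors thins the cells, and Table 1 shows that two of the three conditions are small.

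**Working it through.** **Inputs from the article.** The target is 450, which reproduces as 200 conspicuous plus 250 inconspicuous (Sample size). It rests on a rule of thumb for the structural equation model; no power, alpha or effect size is given for Q3 or Q4. Table 1 (preliminary, n=426) gives:

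- 297 inconspicuous and 129 conspicuous (129/426 = 30.3%);
- 44 males and 85 females among the conspicuous;
- age mean 15.41, SD 2.05;
- in the row "Cystic fibrosis", 28 participants, 7 of them conspicuous;
- 82 with juvenile idiopathic arthritis, 20 of them conspicuous.

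The margins add up: 185+240+1 = 426 and 316+28+82 = 426.

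**Assumptions of this check.** Predictors are normal, alpha is two-sided 0.05, correlations are 0.10 to 0.20, and age, gender and severity are independent within each group.

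**Information kept by a split.** For a normal predictor cut so that a proportion p lies on one side, the share kept is φ(z_p)² / [p(1−p)]. For k groups with boundaries a and b it is the sum of (φ(a)−φ(b))² / P(group).

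| Split | Kept | Lost |
|---|---|---|
| Median | 2/π = 0.637 | 36% |
| 60/40 | 0.622 | 38% |
| Observed 70/30 | 0.577 | 42% |
| Tertiles | 0.793 | 21% |
| Quartiles | 0.861 | 14% |
| Age at 16 | 0.618 | 38% |
| Age at 18 | 0.348 | 65% |

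The 70/30 row is equivalent to using 0.577 × 426 = 246 participants.

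**Power.** By Fisher's z, power = Φ(√(N−3)·atanh(r) − 1.96), with r multiplied by the square root of the share kept when the predictor is split. At N=450:

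| r | Continuous | Median split | 70/30 split |
|---|---|---|---|
| 0.10 | 56% | 39% | 36% |
| 0.15 | 89% | 72% | 68% |
| 0.20 | 99% | 93% | 90% |

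Example at r=0.10: √447 = 21.14. Continuous: 21.14 × 0.1003 − 1.96 = 0.16, so 56%. Median split: r becomes 0.10 × √0.637 = 0.0798, and 21.14 × 0.0800 − 1.96 = −0.27, so 39%.

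**Cells, Table 1 counts.**

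- The four named predictors at two levels each (male/female) give 16 cells. With median splits of age and severity, the smallest is conspicuous males, 44/4 = 11.
- With tertiles of age and severity it is 44/9 = 4.9.
- With age cut at 18 (about 10.3% at or above, by the normal approximation) and severity at the median, it is 44 × 0.103/2 = 2.3.
- With diagnosis as a fifth, three-level factor there are 2×2×2×2×3 = 48 cells. Conspicuous cystic fibrosis averages 7/8 = 0.9 per cell, and conspicuous arthritis 20/8 = 2.5.

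**The case against.** The strongest reply is that no categorisation of age or condition severity is written down. A model described as ANOVA can carry covariates, and the article foresees this: Covid-19 distress, measured on 0–100 sliders, is to be controlled for in all analyses if it is associated with adjustment. Factor coding is also detail that an article may leave to a fuller plan. This stands in part. A reader might infer that the plan forces cut points, and the text does not support that. But the Covid-19 sentence concerns a nuisance variable. It does not say that the hypothesised predictors enter as continuous terms, and the named method points the other way.

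A reader might also infer near-empty cells as a consequence of the plan. That does not follow from the four predictors in the hypotheses, where median splits leave about 11 in the smallest male/female cell. It needs diagnosis to be crossed in, a skewed cut or more levels. Diagnosis is a plausible condition-related factor, since the article lists the condition itself among its condition-specific variables, but neither hypothesis names it and full crossing is not stated. A main-effects model would not depend on filled cells.

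A single loss figure of about 40% would likewise be too strong, because it holds only for a two-level cut near the middle. The 42% figure is approximate in a further way: the conspicuous group comes from an either-or rule on two scores, not from one normal score. At r=0.20 the power cost is modest, 99% against 93%.

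Nor is it certain that the registry markers are the severity variable. The article lists severity separately from them and also collects a subjective rating asked across conditions.

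Finally, the Q2 regression already uses such factors as independent variables, and the structural equation models add covariates. But the Q2 regression has only quality of life as its outcome, so it does not cover adaptation or the one-year course. The article assigns those comparisons to the ANOVAs.

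**Conclusion.** The method named for Q3 and Q4 fits the graded hypotheses poorly, and a better one is available from data already collected. The size is conditional. If age or severity is dichotomised near the middle, 36–42% of its information is lost; with three or four levels the loss is 14–21%. At N=450 a median split costs 17 percentage points of power at both r=0.10 (56% to 39%) and r=0.15 (89% to 72%). These figures assume normal predictors, a two-sided alpha of 0.05 and the stated correlations, none of which the article gives.

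Sparse cells are a second, more conditional risk. It is serious for cystic fibrosis if diagnosis is fully crossed (about 0.9 conspicuous participants per cell) and mild otherwise. The counts are preliminary and will shift as recruitment closes. The point deserves correction before analysis, but it does not affect the main structural equation models.

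**What to change.** - **Q3:** replace the ANOVAs by linear regression or ANCOVA.
- **Q4:** use a mixed model or repeated-measures general linear model with predictor-by-time terms, which test the course directly.
- **Predictors:** enter age, the PHQ-9 score, the GAD-7 score and condition severity as continuous terms. For severity, name either the common subjective rating or the registry markers standardised within condition and aligned so that higher always means more severe.
- **Factors:** enter gender and diagnosis as main effects, include only interactions named in advance, and say how the one non-binary participant is handled.
- **Group contrast:** keep conspicuous versus inconspicuous as a stated comparison in a separate model. It is the design's grouping factor, but it is derived from the same PHQ-9 and GAD-7 scores.

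The cost is a change of wording and a linearity check by a quadratic or spline term. The multicollinearity check already planned covers entering both symptom scores together. No new data are needed.
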